### Participant timeline {13}

This study’s participant recruitment began in August 2021 and is still ongoing. The recruitment process is expected to be completed in March 2022. The intervention, data analysis, final report, and knowledge translation activities will take place between March 2022 and December 2023. This manuscript was designed according to SPIRIT reporting guidelines [17].

Time schedule of enrolment, intervention, and assessments is illustrated in Table 1 according to the SPIRIT Guideline.

**Table 1 Tab1:** Participant’s timeline in Mehrpishegan study

	Study period				
	Enrolment	Allocation	Post-allocation		Close-out
Timepoint	−t1	t0	t1	t2	t3
**Enrolment:**					
Eligibility screen	X				
Informed consent	X				
Learning to use the website and assign a username and password	X				
Allocation and randomization			X		
**Interventions:**					
**Intervention** (first 3 months)			X		
**Intervention** (second 3 months)				X	
**Assessments:**					
Baseline sassement: Demographic questionnaire + Dass-21		X			
Assessment (T1 Dass-21				X	
Assessment (T2): Dass-21					X

### Sample size {14}

The study population consists of informal primary caregivers of the elderly in the South Tehran, who have the willingness to participate. The sample size has been calculated using PASS 15.0.5 software. Based on literature [18] and using Cohen’s formula (expecting the average effect size) with a coefficient = 0.5 φ [19], for both of the intervention and control groups (63 people), taking into account the power of 80. The effect size is 0.50 and the significance level (alpha) will be 5%, the probability of drop-out and withdrawal of the study is 20%, equivalent to 80 people in each group, and the total will be 160 people.

### Recruitment {15}

We will seek help from the South Tehran Health Center, hospitals, and other organizations in the area to cooperate to promote adequate enrolment. We will explain the aims and process of the study to their staff. We will ask them to advertise our study on virtual social networks and invite caregivers to participate in it. We will continue advertising until we reach the expected sample size. Furthermore, we will review the health records of elderly people in order to identify dependent elderly people and their caregivers, which were compiled in the South Tehran Health Center. Informal caregivers will be invited to participate according to inclusion criteria using telephone invitations. The purpose of the study, possible pros and cons of participation in the study, assurances of confidentiality, and the process of conducting the study will be explained to the caregivers. Also, the Mehrpishgan website will be introduced. If the individuals are interested in participating in the study and are eligible, they will receive a username and password and will be asked to complete the online consent form and the baseline measurement on the website. Before the commencement of the intervention, participants who will be in mild and moderate categories (based on DASS-21 scores) will be randomly assigned to one of the intervention or control groups.

Afterwards, participants in the intervention group will be asked to establish their activities in the web-support group for 6 months. At the end of the third month and sixth month, T1 and T2 assessments will be conducted in both intervention and control groups.

The control group will not be exposed to any intervention during the study. However, after completing the T2, they can use facilities of the website (Fig. 1).

**Fig. 1 Fig1:**
[figure not shown]
Participations flow diagram

## Assignment of interventions: allocation

### Sequence generation {16a}

Randomization sequences will be generated using the online sealed envelope website (https://www.sealedenvelope.com/). To generate this randomized sequence, firstly a Software of Statistics and Data Sciences statistical (STATA) will be generated on sex variable; then, based on block size of four, all individuals will be allocated to two equal groups (20 blocks). A statistical consultant, independent of the research team, will generate a random sequence.

### Concealment mechanism {16b}

For each person in each group, anonymous codes will be generated by employing the concealment code. Instead of the sequence of intervention groups as A and B, the concealment codes will be provided to the researchers in the field, and the randomization sequence will be blind during random assignment.

### Implementation {16c}

Potential participants will be invited to the study by the staff of the above-mentioned centers. HH will use sealed envelope website to produces the allocation sequence. The study groups will be revealed only to the FR.

## Assignment of interventions: blinding

### Who will be blinded {17a}

This will be a single-blind study. Primary caregivers will be invited to the study through the researcher’s phone call. Then, invited caregivers who meet inclusion criteria will register on the website and fill in the baseline measurement (DASS-21). The score will be calculated by the website plugin automatically at the end of the questionnaire. Based on the scores, participants in the mild and moderate categories will be informed that they will be randomly divided into two groups: the intervention group, who will have access to the website’s support group for six months, and the control group, who will only have access to the general interface of the website during the study. The data will be entered to SPSS software and delivered in coded form (first and second group) to data analyst to avoid bias in the outcome evaluation, so only the data analyst will be blinded.

### Procedure for unblinding if needed {17b}

This is not applicable.

## Data collection and management

### Plans for assessment and collection of outcomes {18a}

Data will be collected in three stages: before the intervention (T0), by the end of the first 3 months (T1), and by the end of the second 3 months (T2) after the intervention, using a 22-item demographic questionnaire and the online standard Persian-version of the 21-item DASS questionnaire.

The demographic questionnaire consists of 22-items including four main parts: (1) demographic characteristics of the caregivers including age, gender, educational status, occupation, marital status, place of residency, health status, and ethnicity; (2) activities of the caregivers including passing an elderly care training course, using comprehensive health care services, social activities, and types of services received for care assistance; (3) records on how to provide care, such as duration of care, daily life activities, instrumental daily life activities, number of people receiving care, and availability of the needed care; and (4) demographic characteristics of the elderly, including age, gender, health status, insurance, and ethnicity.

The DASS-21 Standard Depression, Anxiety, and Stress Questionnaire consists of 21 items prepared by Lovibond and Lovibond in 1995. The validity and reliability of the Persian-version of the questionnaire have been checked among Iranian population in some previous studies [20–22].The questionnaire is designed on a 4-point Likert scale: zero = at all (never), 1= low (sometimes), 2 = medium (often), and 3 = high (almost always) options. The lowest score for each question is zero, which indicates the best situation, while the highest score is three, which indicates the worst condition. To calculate the final score on each scale, the set of scores is multiplied by two, and the participant is placed in one of the normal, mild, moderate, severe, very severe subgroups specific to that scale. The points are calculated by the website plugin and are provided to the participant automatically at the end of the test.

### Plans to promote participant retention and complete follow-up {18b}

Study participants will be invited to the study by telephone and will receive full information about the study, how to use the website, and the importance of completing it. Questionnaires are uploaded on the website so that each participant can answer the questions accurately without the stress of time constraints. At each stage, participants are reminded via SMS to complete the questionnaires. During the study period, researchers review the answers and contact participants, if necessary. Researchers will also be available to answer potential questions via the website or by phone. Intervention team members will be notified and encouraged to join the online chatroom and use site updates related to the intervention via SMS.

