#### Strategies to improve adherence to interventions {11c}

Logging in to the website will be through a personal username and password, and approval of the administrator (FR) in order to maintain confidentiality and protect adherence. Participants in the interventional group will learn how to properly use different parts of the website such as support group, forums, and educational content. In addition, participants will be reminded to join the group and forums at the appropriate times via short message service (SMS)/notifications. Participants will be encouraged to take part in discussions and read the summary file prepared by the facilitator. Also, the researchers will participate in the support group and forums in order to increase their common sense and oversight. Participants will be able to send their comments and suggestions through the website and contact the researcher/facilitator in case of any problems.

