### Outcomes {12}

This study has three primary outcome variables (depression, anxiety, and stress) that are going to be measured by the DASS-21 scale three times during the study: before (T0), by the end of the first 3 months of the intervention (T1), and by the end of the second 3 months (T2) after the intervention. The effect of the web-based support group on depression, anxiety, and stress in the intervention and control groups will be assessed and compared before and after the intervention. The difference in the mean scores of the outcomes will be assessed.

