### Data management {19}

All information, including informed consent forms and demographic characteristics, will be collected through Mehrpishegan website in the form of electronic case report forms (eCRF). The questionnaires are also completed online by the participants. The database will be backed up every day. Total backups will be done weekly and monthly. A password system will be utilized to control access to the study data.

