### Composition of the coordinating center and trial steering committee {5d}

This study is part of a PhD thesis in Health Education and Promotion program, so the main responsibility for preparing the protocol, and implementation, including identification, recruitment, data collection, and implementation of the intervention, along with following the study participants and publishing study reports, is the responsibility of the student (F.R.).

In addition to the student, the members of the research team include the supervisors and advisors (two professors in Health Education and Promotion, one epidemiologist with a specialty in clinical trial projects, and one psychiatrist). The project supervisor and advisors are responsible for reviewing the protocol, monitoring the proper implementation of the project from a scientific and executive point of view. They are also responsible for the progress of the study, agreeing to change the protocol if necessary, and confirming the accuracy of the results for publication.

Budget management is done jointly by E.Sh and F.R. E.Sh will provide the research findings to the Vice Chancellor for Research and the Vice Chancellor for Health at Tehran University of Medical Sciences. In the event of any danger or unwanted damages, E.Sh and F.R. are responsible for reporting it to the ethics committee.

Furthermore, the project will benefit from the cooperation of experts in software for technical support of Mehrpishegan website, psychologists, geriatricians, and nutritionists to provide educational content, facilitate the support group, and answer questions from participants.

The main research team members will meet at the end of each trial phase and whenever needed. The other members will be in touch throughout the research and will meet as needed at each step.

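### Staff who know the allocation may review self-reported outcome answers and contact participants during the trial, an avoidable route to influenced T1 and T2 reporting that analyst blinding does not close

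*Protocol article*

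**What the plan says.** All references are to the protocol article.

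- **Outcomes {12}:** "This study has three primary outcome variables (depression, anxiety, and stress) that are going to be measured by the DASS-21 scale three times".
- **Data management {19}:** "The questionnaires are also completed online by the participants".
- **Plans for assessment and collection of outcomes {18a}:** "The points are calculated by the website plugin and are provided to the participant automatically at the end of the test". Scoring is therefore automatic.
- **Plans to promote participant retention and complete follow-up {18b}:** "At each stage, participants are reminded via SMS to complete the questionnaires". The next sentence is "During the study period, researchers review the answers and contact participants, if necessary".
- **Who will be blinded {17a}:** data go to the analyst in coded form "to avoid bias in the outcome evaluation, so only the data analyst will be blinded".
- **Implementation {16c}:** the study groups are disclosed to one team member only, the student who runs the trial.
- **Composition of the coordinating center and trial steering committee {5d}:** that student's responsibilities are listed as "including identification, recruitment, data collection, and implementation of the intervention", together with following the participants.
- **Strategies to improve adherence to interventions {11c}:** "the researchers will participate in the support group and forums in order to increase their common sense and oversight".
- **Confidentiality {27}:** the research team holds the key linking study codes to participants while the study runs.

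**The concern.** With a self-reported outcome, the participant's answer is itself the outcome assessment. If someone who knows the arm, and who works with one arm for six months, can read those answers and contact the respondent during follow-up, reporting is open to influence from the people running the treatment. That influence could differ between arms without anyone intending it.

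The blinding section presents coded data as the protection against bias in outcome evaluation. Coding acts only after the answers have been given, so the plan credits it with a protection it cannot provide at the point of reporting. At stake is the between-arm difference on all three primary outcomes. Participants in a support-group trial cannot realistically be blinded. Giving intervention staff access to outcome answers is a separate exposure, and an avoidable one.

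**Working it through.** The documents give no figure for this bias, so the check is mainly a reading of the sections against each other.

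**1. Which answers are reviewed?** The sentence directly before the one on review concerns completing the questionnaires at each stage. The questionnaires are the demographic form and the DASS-21. The DASS-21 is given at T0, T1 and T2, so the answers under review include the primary outcomes.

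**2. Which time points matter?** Allocation follows the baseline measurement (Explanation for the choice of comparators {6b}), and baseline scores are needed for entry (Recruitment {15}). Review at T0 precedes allocation and cannot depend on arm. The exposure is at T1 and T2.

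**3. Do the reviewers know the arm?** {18b} says only that researchers do the review. {17a} blinds nobody but the analyst. {16c} and {5d} together place knowledge of allocation, data collection, implementation of the intervention and follow-up with one student. Under {11c}, researchers present in the group and forums can see who belongs to the intervention arm. Under {27}, study codes do not hide identity from the team.

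**4. Do the stated safeguards reach the problem?**

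| Safeguard | What it prevents | Does it stop influence on T1 and T2 answers? |
|---|---|---|
| Coded data for the analyst {17a} | Arm-driven choices in the analysis | No, the answers already exist |
| Automatic scoring {18a} | Scoring error or judgement | No, it scores whatever is entered |
| Concealment codes {16b} | Foreknowledge at random assignment | No, they concern assignment |
| Passwords {19} | Unauthorised access | Not as described: no limit on the research team's access to answers is stated |
| Independent audit {23} | Data-quality and conduct problems | No, it does not govern who contacts participants |

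**5. By what route could answers change?** A contact prompted by T1 answers could colour T2 answers. A participant who knows that group researchers read the responses could answer differently at T1 or T2. Both are inferences. The documents do not say that submitted answers can be reopened or edited.

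**6. Sample size, as background.** With d = 0.50, power 80% and alpha 5% (two-sided assumed), n = 2(1.960 + 0.842)²/0.50² = 62.8, so 63 per group, as stated in Sample size {14}. Allowing for 20% dropout, 63/0.80 = 78.75, so 79. The t-test version needs 64, and 64/0.80 = 80. The plan's 63 and 80 reproduce and are not in dispute.

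**7. Illustration only.** Suppose there is no true effect and reporting shifts the arm difference by b SD. For one outcome, the two-sided 5% rejection probability is 1 − Φ(1.96 − b/SE) + Φ(−1.96 − b/SE), with SE = √(2/n).

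| Assumed b | n = 63 per group (SE 0.178) | n = 80 per group (SE 0.158) |
|---|---|---|
| 0 | 5.0% | 5.0% |
| 0.1 | 8.7% | 9.7% |
| 0.2 | 20.2% | 24.4% |

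The values of b are assumptions about a whole-arm mean. If only 20% of an arm were contacted (also an assumption) and the influence came only through contact, each contacted person would have to shift by 0.1/0.20 = 0.5 SD to 0.2/0.20 = 1.0 SD to produce them. The same table would apply to any unblinded self-report trial, so it does not measure the effect of this sentence.

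**The case against.** The strongest reply is that the sentence sits under retention and complete follow-up, between an SMS reminder and an offer to answer questions. The natural reading is then a check for missing forms, and a condensed article may leave query procedures to the full protocol. That reading may well be what was intended. But reminders are already covered by the preceding sentence, and the text says that answers, not completion, are reviewed. What is criticised is an open-ended permission that the article states, not a detail it omits.

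Four stronger readings are tempting, and the documents do not support them:

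- **Staff discuss or correct answers with participants.** {18b} gives no content for the contact and does not mention a telephone call about answers. The questionnaire is scored and the score returned at the end of the test. Nothing says it can be reopened.
- **The group facilitator reviews the answers.** Intervention procedure makes the facilitator a psychologist, and {5d} lists psychologists among the cooperating experts. {18b} refers to researchers. Nor is every researcher formally told the allocation: {16b} gives field researchers concealment codes and {16c} discloses the groups to one person. The point rests on that person's combined roles and on researchers being present in the group.
- **The intervention arm is affected more.** This is plausible given the contact in the group, but {18b} describes review and contact for participants generally.
- **A positive result would be uninterpretable because of this sentence.** Reporting bias from unblinded participants exists with or without it and would survive the fix.

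The objection that answers may be needed for participant welfare stands, and it shapes the fix. {11b} and {11d} make participants' mental-health status relevant to continuing in the study, and {22} requires all adverse events to be collected.

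**Conclusion.** The point holds as an avoidable weakness in the design. The plan allows researchers to review primary-outcome answers and contact participants during follow-up, without confining this to completeness or to staff unaware of allocation. The only blinding it offers acts after the answers have been given. This rests on reading the reviewed answers as including the DASS-21, which the adjacent sentence supports, and on the student's combined roles, which are stated.

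The size of any influence cannot be estimated from the documents. The rejection rates above are conditional on assumed shifts and are not an estimate for this trial. The route adds to an unavoidable reporting bias and is not its only source. The change is worth making because it is cheap and removes the part that can be removed.

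**What to change.** **In {18b}**, replace the sentence on reviewing answers with wording such as: *The website checks completeness automatically and requires all items before submission; submitted answers are locked. Until database lock, staff who know the allocation or take part in the intervention see only a completed / not completed flag for T1 and T2. Contact about questionnaires is limited to a scripted reminder, identical in both arms.*

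**Welfare and adverse events.** If answers are also to be reviewed for the purposes of {11b}, {11d} or {22}, state this separately, with its purpose, and assign it to an existing team member who does not take part in the support group or forums.

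**In {17a}**, state that coding the data for the analyst protects the analysis only, not the outcome reporting.

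**Cost.** One access setting and a few sentences. Intervention description {11a} already plans access levels by user type, and {19} a password system. One team member has to be kept out of the intervention if a welfare review is wanted. The small downside is that allocation-aware staff can no longer query implausible answers with participants.

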### Data management {19}

All information, including informed consent forms and demographic characteristics, will be collected through Mehrpishegan website in the form of electronic case report forms (eCRF). The questionnaires are also completed online by the participants. The database will be backed up every day. Total backups will be done weekly and monthly. A password system will be utilized to control access to the study data.

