#### Criteria for discontinuing or modifying allocated interventions {11b}

Termination of care tasks (change of care status to non-primary caregiver, death or recovery of the elderly); the participant’s request; leaving the support group and not using the website; undergoing any kinds of medical treatments; emergence of an adverse issue during the study that seriously affects the individual’s mental health, such as divorce or death of close relatives; or any behavior that threatens or harms other participants will result in exclusion from the study or discontinuing the intervention.

To estimate the efficacy, all participants will be analyzed according to randomization assignment (ITT approach) as a full analysis set (FAS) population. In addition, per protocol (PP) approach will be done as well.

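### T1 and T2 DASS-21 are collected only through the website that delivers the intervention, and the plan does not say they are still sought after a participant stops, so intervention-arm stoppers risk going unmeasured

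*Protocol article*

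**What the plan says.** The outcome route is stated, not left to inference. Plans for assessment and collection of outcomes {18a} specifies an online DASS-21 scored by the website plugin. Retention {18b} says "Questionnaires are uploaded on the website so that each participant can answer the questions accurately". Data management {19} says all information is collected through the site and that "The questionnaires are also completed online by the participants". No other route for T1 or T2 is described. Access is controlled: under {11c}, "Logging in to the website will be through a personal username and password, and approval of the administrator".

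The Intervention procedure section defines the intervention as use of this same website: weekly chatroom sessions of 60 to 90 minutes, assignments and forums. Controls see only the general interface.

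Section {11b} lists "leaving the support group and not using the website" with other events that "will result in exclusion from the study or discontinuing the intervention". It does not say which consequence follows which event, or whether T1 and T2 are still collected. The next paragraph says "all participants will be analyzed according to randomization assignment (ITT approach) as a full analysis set (FAS) population". Statistical methods {20a} and the missing-data section {20c} repeat the intention-to-treat commitment, and {20c} fills gaps by simple linear regression.

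As mitigation, {18b} provides SMS reminders to complete the questionnaires at each stage, and researcher contact where needed. Recruitment {15} plans T1 and T2 in both arms.

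**The concern.** An intention-to-treat analysis needs outcomes from people who stop the intervention. Here the treatment and the measuring instrument share one site. An intervention participant who has given it up must return there to be measured. If the exclusion branch of {11b} is applied, that participant may not be measured at all.

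Controls have no sessions or assignments to abandon and cannot leave a support group they never joined. This route to a missing outcome therefore exists in one arm only. If those lost do worse than those who stay, the intervention arm's T1 and T2 means describe mainly the people who persisted, and the effect is overstated. Regression imputation corrects only the part of the difference that its predictors explain. If few stoppers are observed, the fitted model reflects mainly those who stayed.

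**Working it through.** **Step 1: the passages side by side.**

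| Question | What the protocol article gives |
|---|---|
| Where is the DASS-21 completed? | On the website only ({18a}, {18b}, {19}) |
| What is the intervention? | Use of the same website (Intervention procedure) |
| What follows leaving the group and not using the site? | Exclusion from the study, or discontinuing the intervention ({11b}) |
| Are T1 and T2 collected after that? | Not stated |
| Who is analysed? | Everyone as randomised ({11b}, {20a}, {20c}) |

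Exclusion from the study and analysis of everyone randomised are compatible only if outcomes continue to be collected, or if the missing ones are all imputed.

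**Step 2: the plan's own figure.** Sample size {14} uses effect size 0.50, alpha 5% and power 80%. The two-sided normal approximation gives 63 per group (power 0.801), and 63/0.8 = 78.75, i.e. 79. The t-test version gives 64, and 64/0.8 = 80. The stated 63 and 80 per group are reproduced within rounding, so the planned effect of 0.50 is used as the yardstick.

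**Step 3: illustrative bias in the intervention mean.** None of these inputs is in the protocol; all are assumptions.
- q = share of the intervention arm that stops using the site: 20% (16 of 80), range 10% to 30%.
- 80% of stoppers have no T2 score; all who persist have one.
- s = how much worse stoppers are than those who persist: 0.3 to 0.5 SD.
- Control missingness is unrelated to outcome.
- Observed scores only, before any imputation.

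Relative to those who persist, the whole arm is worse by q·s. Among those observed, stoppers make up 0.2q/(1 − 0.8q), so the observed mean is worse by only 0.2qs/(1 − 0.8q). Hence

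bias = qs − 0.2qs/(1 − 0.8q).

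For q = 0.2 and s = 0.3: 0.060 − 0.012/0.84 = 0.060 − 0.014 = 0.046.

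| q | s = 0.3 | s = 0.5 |
|---|---|---|
| 0.10 | 0.023 | 0.039 |
| 0.20 | 0.046 | 0.076 |
| 0.30 | 0.066 | 0.111 |

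As a share of 0.50, the 20% row is 9% to 15% (0.046/0.50 and 0.076/0.50). The corners of the table are 5% and 22%.

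**Step 4: what moves the result.** If no stopper is measured, the second term vanishes and bias = qs, e.g. 0.2 × 0.5 = 0.10. If controls lose the same share of people with the same deficit, the two biases cancel in the difference. If control losses are the more selective, the sign reverses.

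**Step 5: precision.** Power for 0.50 is 0.807 with 64 measured per arm. It is 0.780 with 56 intervention and 64 control, and 0.745 with 48 and 64. Extra loss in one arm costs some power, but bias is the larger worry.

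**The case against.** A reader might infer that people who stop the intervention necessarily stop being measured. The protocol does not say so. Section {11b} offers discontinuing the intervention as an alternative to exclusion, {15} plans T1 and T2 in both arms, and the reminders and researcher contact in {18b} are not limited to active users. The stop event is also a joint one: leaving the group and not using the site.

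A reader might also infer that missingness will fall mainly on the intervention arm. That is plausible but unproven. Controls know their allocation and have little to bring them to the site for six months, while the intervention arm gets additional SMS contact. Controls complete T1 and T2 on the same site without any intervention facility, so the questionnaire can be answered without entering the chatroom or forums. A lapsed user needs one prompted visit.

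Finally, the bias figures rest on assumptions and ignore imputation, which can use the baseline DASS-21. Back-up modes of completion are also detail that an article may leave to the full protocol.

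These points remove any claim of certainty or of a known direction. They do not remove the risk. The article says affirmatively that all data go through the site, the reminders lead back to that site, and {11b} leaves follow-up after a stop event unsettled beside a promise to analyse everyone.

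**Conclusion.** The point holds as a risk that the text creates and does not close. The only described outcome route runs through the website that is the intervention. One listed consequence of giving it up is exclusion, and continued T1 and T2 collection is not stated. Because leaving the support group can occur only in the intervention arm, missingness may differ by arm and be related to outcome.

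Neither size nor direction can be established from the document. The range of 0.02 to 0.11 SD is illustrative and depends on the assumed stopping rate, non-response among stoppers, their deficit and uninformative control losses. About a fifth of the planned effect is reached only at the most adverse corner. This should be changed before T1; confidence in its practical importance is medium.

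**What to change.** 1. State that T1 and T2 are sought from every randomised participant, whatever their website use or intervention status.
2. Reconcile the exclusion wording in {11b} with the full analysis set in {11b} and {20a}. Which events stop the intervention is for the investigators; what the analysis needs is that stopping and outcome collection are kept separate.
3. Send T1 and T2 to both arms by an individual, secure SMS link that opens the self-completed questionnaire without entering the support-group site. Keep it active after website access ends. It must be consistent with the password and confidentiality provisions in {11c}, {19} and {27}.
4. If telephone completion is offered at all, make it a last resort under the same rule in both arms. Record the mode and date, and add a sensitivity analysis without those scores. Section {17a} blinds only the data analyst, so callers could know the allocation while administering a self-report scale.

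The cost is small: one stand-alone form in the existing content management system and use of the SMS channel already planned. The downside is a possible mode or unblinded-interviewer effect, confined to any telephone completions.
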